**Details of IRB approved project modifications begin on pg. 10**

**Overview of Study Design:**

The long-term objective of the current research is to improve treatment outcomes for individuals with comorbid PTSD and alcohol abuse and dependence (AUD). Prior research has established that PTSD and AUD are frequently comorbid. Although combined treatments have been developed, they are complex and lengthy with mixed results as to their efficacy. Excellent treatments exist for PTSD or AUD alone, however, we do not know to what extent these treatments are effective in treating comorbid symptom presentations. To address this research gap, we will evaluate a widely accepted treatment for each respective disorder; Cognitive Processing Therapy (CPT) for PTSD and Relapse Prevention (RP) for AUD. Our purpose is to evaluate changes in both PTSD symptoms and alcohol use and cravings associated with CPT or RP treatment in individuals with PTSD/AUD, along with mediators and moderators of outcomes. We are building on our prior work using a daily telephone Interactive Voice Response (IVR) system to test models of self-medication and the sequence of symptom change for both primary and secondary symptom targets associated with each therapy. The study will randomize 235 PTSD/AUD participants recruited from the VA and from the community to CPT, RP, or IVR assessment only (AO). Those in the AO condition will be re-randomized after IVR assessment to either CPT or RP. Individuals will be assessed pretreatment, immediately post-treatment, 3-, 6-, 9- and 12-months post-treatment. We also monitor symptoms with daily IVR assessments throughout the initial treatment phase.

The study has three aims:

1. To evaluate the efficacy of CPT and RP in reducing primary and secondary symptom targets for PTSD/AUD.
2. To examine the mechanisms of symptom change in each therapy using daily IVR assessments.
3. To conduct exploratory analyses, which will examine the moderators of treatment improvement and outcomes.

Primary outcome measures: PTSD severity and diagnostic status are assessed via the Clinician Administered PTSD Scale (CAPS) interview and alcohol use is assessed with Form 90 at all follow-up time-points. In addition, data on PTSD, drinking, and potential mediators of change are collected daily during the pre-treatment week-long baseline period and the six-week treatment phase in order to evaluate the sequence of symptom change associated with each condition.

We hypothesize that both CPT and RP will demonstrate stronger effects in reducing alcohol use and PTSD symptoms than assessment only (i.e., daily symptom monitoring) over the course of the 6-week treatment period and at the immediate post-treatment. After the post-treatment assessment, the assessment only group will be randomized to either CPT or RP. We also hypothesize that each therapy will have the strongest effects on reducing that therapy’s primary symptom targets (PTSD symptoms for CPT; alcohol use and cravings for RP) at immediate, 3-, 6-, 9-, and 12-month post-treatment assessments and over the course of therapy. Through this study we will also evaluate the mechanisms or mediators of change. We hypothesize that individuals in the CPT condition will demonstrate initial changes in PTSD symptoms and that alcohol will decrease as PTSD symptoms decline; changes in PTSD symptoms will mediate changes in alcohol use and cravings. Similarly, we hypothesize that for those in the RP condition the initial changes will be seen for alcohol use and cravings with PTSD symptom severity declining as treatment continues; changes in self-efficacy and distress tolerance will mediate PTSD symptom changes. Exploratory analyses will evaluate whether specific participant characteristics (e.g., severity of AUD, severity of PTSD, motivations for drinking) help to explain or moderate treatment responses.

**Setting**

This research is being conducted at the University of Washington and VA Puget Sound Health Care System—Seattle campus. The UW Center for the Study of Health and Risk Behaviors (CSHRB) is leading data collection and treatment conducted at the UW’s Harborview Center for Sexual Assault and Traumatic Stress (HCSATS) and the Addiction Treatment Center (ATC) at the Seattle campus of the VA Puget Sound Health Care System.

Each site has private individual meeting rooms where participants undergo assessment and therapy provided by trained professional staff. Audio recordings of all in-person sessions are stored on a secure server with restricted access. Assessments are conducted in person, over the internet as well as by telephone through an Interactive Voice Response system (IVR).

**Participants**

Participants, comprised of active duty soldiers, veterans and civilians, will be 235 males and females over age 18 (with half to be seen at HCSATS and half at VAPSHCS) with a current primary DSM-V diagnosis of PTSD and of AUD. They must endorse alcohol consumption that meets either the PAST MONTH criteria (i.e., either reports >14 drinks per week for women or >21 drinks per week for men for at least 2 weeks in the past 30 day period or at least 2 days of heavy drinking in the past 30 day period (4+ drinks for women and 5+ drinks for men) OR the PAST 90 DAY criteria (i.e., some drinking in Past 2 Weeks AND EITHER (alcohol consumption of >14 drinks per week for women or >21 drinks per week for men for at least 2 weeks in the past 90 day period or at least 2 days of heavy drinking in the past 90 day period (4+ drinks for women and 5+ drinks for men)).

**Study Conditions:**

**Assessment Only (AO)**

Participants in the Assessment Only (AO) condition complete daily monitoring by phone. Each day, they answer questions about their drinking, anxiety, and trauma symptoms via an automated phone system. Every week at a pre-arranged time a clinical staff member calls AO participants to check on how they have been doing and to address any safety concerns. These phone calls typically last between 5 and 15 minutes. After completing the monitoring period, AO participants are re-randomized to one of the two treatment conditions — either Cognitive Processing Therapy (CPT) or Relapse Prevention (RP).

**Cognitive Processing Therapy (CPT)**

Cognitive Processing Therapy (CPT) is a cognitively oriented approach to treating PTSD symptoms developed in the 1980’s. The goal of CPT is to help participants address memories, thoughts, and emotions about the traumatic event. In CPT participants will talk about how their beliefs about safety, trust, control, self-esteem, other people, and relationships can be affected by trauma. Participants learn to find a better balance between the beliefs they had before and after their trauma. These skills can also be applied to help with other challenges, such as urges to drink or the use of alcohol to avoid trauma-related thoughts or triggers. Participants use in session practice and between session homework to develop these skills and apply them in their day-to-day lives.

**Relapse Prevention Therapy (RP)**

Relapse Prevention (RP) is a behaviorally oriented approach to treating substance use problems developed in the 1980’s. The goal of RP is to help participants effectively address the difficulties in their lives that contribute to substance use. RP teaches participants how to identify and cope with their personal triggers for alcohol use, which could include PTSD symptoms. Through active role playing in session and examination of recent situations, as well as homework practice, participants learn new coping skills to address their personal high risk situations. Participants self-monitor their drinking and triggers throughout treatment. Specific topics for sessions include understanding and managing anger, communication and assertiveness skills, and coping effectively with negative feelings and thoughts.

**Inclusion and Exclusion Criteria:**

**Inclusion criteria**

- Age  18 years
- English fluency
- Capacity to provide informed consent
- Would like to participate
- Desire to abstain from alcohol or reduce alcohol use
- Current DSM-V diagnosis of PTSD
- Current DSM-V diagnosis of AUD
- Minimum drinking levels for inclusion in study:

Past Month Criteria:

- Reports >14 drinks per week for women or >21 drinks per week for men for at least 2 weeks in the past 30 day period

OR

At least 2 days of heavy drinking in the past 30-day period (4+ drinks for women and 5+ drinks for men.

OR

Past 90 Days Criteria: Must have done some drinking in Past 2 Weeks

**AND**

- Either alcohol consumption of >14 drinks per week for women or >21 drinks per week for men for at least 2 weeks in the past 90 day period

OR

At least 2 days of heavy drinking in the past 90-day period (4+ drinks for women and 5+ drinks for men)

**Exclusion criteria**

- Unwilling or unable to commit to regular weekly attendance at therapy appointments
- Taken Antabuse (not merely prescribed) over the past 30 days OR starting to take Antabuse over the next 30 days
- Currently in a PTSD or alcohol psychotherapy that involves regular written practice assignments
- Awaiting sentencing or pending incarceration
- Participation in an experimental drug study or any type of addiction study in the past 30 days
- Experienced delirium tremens within past 6 months
- Presence of an uncontrolled psychotic disorder or uncontrolled Bipolar Disorder

in the past 3 months

- Unstable psychiatric medication regimen (medication changes or dose changes in the past 30 days)
- Signs or symptoms of alcohol withdrawal at the time of initial consent
- Suicide attempt or serious self-harm in the past 3 months OR suicidal ideation with intent or plan in the past 2 months.
- Moderate to high risk for homicidality in the past 6 months
- Current relationship involves severe domestic violence victimization within the past 2 months
- Unwilling to provide one collateral contact
- Unwilling to have assessments or therapy sessions recorded
- Unwilling to provide valid SSN

Participants can have received past therapy with the exception of CPT or RP. Supportive individual or group counseling, case management, and self-help programs will be allowed concurrently. Allowing participants to continue with therapy that is non-overlapping with the research therapies offers them the option to continue with established supports and more closely mimics clinical practice.

**Study Design:**

**Recruitment/Preliminary Screening**

Both sites will identify potential participants through pre-screening and those potential participants will be sent an invitation letter with information about study aims, procedures, compensation, and the voluntary nature of research participation. The letter will request that interested individuals contact the HCSATS or VA Research Coordinator for more information about enrollment. A business reply post-card will also be included to allow individuals to opt-out if they do not wish to participate in the study. Those who indicate they are interested in the study will be screened on the telephone. If we do not receive any response within 2 weeks, we will attempt to follow up via phone. Those who do not return the opt out card and do not call the study will be contacted by phone with up to three messages left to ascertain whether they are interested in learning more about the study and possibly completing the telephone screen.

Additionally, study recruitment takes place through print and online advertisements as well as clinician referrals and flyers distributed in the community (in places such as laundromats, libraries, coffees shops and community and treatment centers and other similar gathering places with public bulletin boards).

Interested individuals call the UW Research Coordinator or the VA Research Coordinator and receive an overview of the study from the study staff over the telephone. Those who are interested undergo a phone screening to determine whether he or she likely meets the study inclusion/ exclusion criteria. In total, this call takes 15-20 minutes. The voluntary nature of research study participation is emphasized. If the caller is ineligible after the initial phone screen, they are offered community referrals by phone, mail or email (email allowed at UW only).

If the caller is eligible at the initial phone screen a 2.5 to 3.5 hour baseline appointment is scheduled with them. The UW has the ability to schedule the baseline appointment at either HCSATS or the VA, while the VA can only schedule the appointment at the VA. Additionally, the UW is allowed to communicate by text and email, while the VA is not. If a potential participant requests directions to be mailed to them prior to the appointment, the RC obtains contact information and sends directions.

**Baseline Assessment--Obtaining Informed Consent and Formal Screening**

The informed consent covers the baseline visit in detail including the fact that if eligible, they will be randomized to one of three conditions: 1) CPT, 2) RP, or 3) Assessment only (AO). 80% will be randomized to receive 12 sessions of individual therapy while completing the daily IVR calls and 20% will be randomized to complete 7 weeks of daily IVR calls before receiving one of the two therapies. The baseline consent will give an overview of the rest of the study as well. Participants are reminded that the study is protected by a Certificate of Confidentiality that prohibits disclosure of research information to the courts or legal authorities. Individuals are breathalyzed after signing the consent; they must have a reading of 0.00 BAC or they will be asked to either wait until their BAC drops to 0.00 or to reschedule the appointment.

A consent quiz is administered to confirm that our participants understand the important elements of the consent form and to ensure that they are capable of providing informed consent. After the consent is reviewed, the participant is asked to complete the quiz.  The clinical assessor will review the answers and explain the correct response to each missed item.  If, after this discussion, the participant truly does not seem able to comprehend the correct response to more than 2 items, the clinical assessor uses her clinical discretion to determine if this participant is ineligible because of being unable to properly provide consent.

Demographic and contact information are obtained. Participants are interviewed using the Clinician Administered PTSD Scale (CAPS) and Life Stressor Checklist for PTSD and the Form 90 for substance use disorder. Participants also complete the PTSD Checklist Civilian version (PCL-C), the Patient Health Questionnaire (PHQ-9) to measure current depression, Medical History Interview, Mini International Neuropsychiatric Interview (MINI), Posttraumatic Maladaptive Beliefs Scale (PMBS), Coping Strategies Scale (CSS), Drinking Motives Questionnaire, Family History of Alcohol Problems Questionnaire, Emotion Reactivity Scale and Externalizing Spectrum Inventory (Disinhibition), Penn Alcohol Craving Scale (PACS), Other Mental Health Treatment and Treatment Goal.

Those who are determined ineligible at the baseline appointment are provided with a list of community resources. Those who are determined eligible at the baseline appointment are trained in the use of the IVR system, provided a four digit ID number to use when calling and instructed to begin calling the following day. All participants are paid for this appointment by check sent by mail

**Randomization**

Participants who meet all inclusion/exclusion criteria are randomly assigned to CPT, RP or AO by the UW research coordinator using a randomization table created for the study. An adaptive randomization protocol is used to insure that the two groups are balanced with respect to baseline severity of AUD, severity of PTSD symptoms and gender. Baseline severity of AUD is dichotomized based on presence of Alcohol Dependence with physiological dependence. Baseline severity of PTSD is dichotomized based on Clinician Administered PTSD scale scores > 59, which indicates severe PTSD.

**Safety and Comfort call**

All participants are informed that a clinical staff member will call them the next business day after the baseline appointment. For those who are ineligible at the baseline assessment, the call is made by the clinical assessor and the purpose of the call is to assess for symptom exacerbation from the baseline visit and to provide support and normalization or to intervene clinically as needed. For those who are eligible, the call is made by the participant’s therapist and in addition to assessing for safety, the purpose is to ask about how the first IVR call went and to let him or her know whether s/he was randomized to the AO condition or to start one of the 2 therapies at the end of a week of baseline monitoring. The therapist making the call does not yet know which therapy the participant will receive but they schedule the first appointment or the first AO check-in call for the following week.

**Daily IVR Monitoring**

To better track daily fluctuations in alcohol use and craving as well as PTSD symptoms, this study will utilize daily IVR symptom monitoring. The IVR system is accessed via a toll-free telephone call and is an automated data collection system that captures entries via the telephone keypad. Compliance with the monitoring protocol will be automatically tracked by the IVR system that will be created and maintained by Database Systems Corp.

If participants fail to call the system as scheduled, the study coordinator attempts to contact participants within three working days in order to collect the data verbally and to resolve any difficulties. The IVR data are transferred automatically to a secure website each day and are in a format that is compatible with most statistical software packages, thus eliminating the need for data entry.

IVR data are reviewed daily on business days for safety concerns. If, through their call data, participants indicate a BAC of higher than .35 (calculated using number of drinks consumed and participant’s weight supplied at the baseline appointment) or if their PTSD symptoms increase by 47 or more points from first day of monitoring, clinical staff or PIs follows up to ascertain that the participant is safe.

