**IVR daily monitoring questions**

The IVR protocol consists of 30 primary questions with 25 additional secondary questions that may be asked, depending on the responses to the primary questions. The IVR program automatically blocks invalid responses and alerts the respondent that they need to make a valid entry. Research on mechanisms of change in treatment of PTSD and alcohol use has typically relied on retrospective reconstruction of hypothesized precipitants of alcohol cravings and drinking behaviors. Because of the use of simple pre-post treatment designs or weekly symptom measures these studies make it harder to examine the interrelationships between PTSD and alcohol use during psychotherapy or to better understand both positive treatment outcomes and non-responders. However, researchers examining negative affect and alcohol use and other addictive behaviors like smoking in non-trauma samples have increasingly begun to utilize daily monitoring of symptoms to examine predictors of substance use and lapses.

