**Assessment Only Check-ins and re-randomization**

During the 7-week daily monitoring period, the AO group receives weekly telephone calls from a study therapist to briefly check-in regarding safety and stability. Should marked clinical deterioration be noted either during a telephone check-in or via the daily IVR assessments, participants are carefully assessed regarding whether their continued involvement in the study is safe and the co-PI’s is consulted on this decision. At the end of their 7 weeks of IVR monitoring the AO participants are re-randomized to receive either CPT or RP but will not continue IVR monitoring during treatment. They are re-randomized using a separate randomization table that is balanced with respect to baseline severity of AUD, severity of PTSD symptoms and gender.

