**QUESTIONNAIRES**

| Study Construct/Variables | Study Phase | | | Measurement Scale | | Timeframe |
| --- | --- | --- | --- | --- | --- | --- |
| Inclusion/Exclusion Criteria | |  |  | |  | |
| Demographic information | | B, 12 | discrete, dichotomous, & continuous (19-25 items) | | Current, Past Year & Lifetime | |
| Medical history interview (Delirium Tremens, planned use of antabuse/naltrexone) | | B | dichotomous (13-18 items) | | Current, Past Month & Lifetime | |
| Mini International Neuropsychiatric Interview (MINI) | | B | dichotomous (44-86 items) | | Current, Past 3 Months, Past 6 Months & Lifetime | |
| SHOT | | B | Discrete (3 items) | | Past 6 Months | |
| Life Stressor Checklist | | B, P, 3, 6, 9, 12 | dichotomous & continuous (29-152 items) | | B - Lifetime & Past Year; P1 - since Baseline; P2 - since P1; 3, 6, 9 ,12 - Past 3 months | |
| Tracking | |  |  | |  | |
| Contact form | | B, P, 3, 6, 9, 12 | comprehensive locator information (43-61 items) | | Current | |
| Outcomes | |  |  | |  | |
| Clinician-Administered PTSD Scale (CAPS) | | B, P, 3, 12 | dichotomous & continuous (27-118 items) | | B, 3, 12 - Past Month; P - Past Week | |
| Daily PTSD Checklist-Civilian Version | | IVR | continuous (20 items) | | Past 24 Hours | |
| Form-90 (alcohol and drug) | | B, P, 3, 6, 9, 12 | continuous - days of use & standard drinks (27-67 items) | | B, 12 - Past year, Past Month & Past 90 days; P - Past Week (alcohol and drug use only); 3, 6, 9 - Past Month & Past 90 days (alcohol and drug use only) | |
| Penn Alcohol Craving Scale (PACS) | | B, P, 3, 6, 9, 12 | continuous (5 items) | | Past Week | |
| Alcohol/drug use | | IVR | quantity (2 items) | | Past 24 Hours | |
| Alcohol cravings | | IVR | continuous (2 items) | | Past 24 Hours | |
| Alcohol/drug problems | | IVR | continuous (1 item) | | Past 24 Hours | |
| Health Status (SF-8) | | B, 3, 12 | continuous (8 items) | | B, 3,12 - Past Month | |
| Short Inventory of Problems (SIP) alcohol/drug use | | B, P, 3, 6, 9, 12 | continuous (30 items) | | B, 3, 6, 9 ,12 - Past 3 Months;  P - Past Week | |
| Mediators | |  |  | |  | |
| Coping efficacy PTSD and drinking | | IVR | continuous (3 items) | | Past 24 Hours & Next 24 Hours | |
| Posttraumatic Maladaptive Beliefs Scale (PMBS) | | B, P, 3, 12 | continuous (15 items) | | B, 3, 12 - Current; P - Past Week | |
| Daily Drinking Motives | | IVR | continuous (5 items) | | Past 24 Hours | |

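### The daily PTSD alert requires a 47-point rise on a score whose instrument and range are not named, so it cannot fire for participants who start within 47 points of the maximum

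*Protocol*

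**What the plan says.** The Daily IVR Monitoring section has staff look through the call data each business day for safety concerns and gives two numeric triggers for contact. One concerns estimated blood alcohol. The other concerns PTSD: "if their PTSD symptoms increase by 47 or more points from first day of monitoring, clinical staff or PIs follows up". The sentence does not say which score is meant, what values it can take, or how 47 was chosen.

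The Questionnaires table lists one PTSD symptom measure collected by IVR, the "Daily PTSD Checklist-Civilian Version", with 20 items covering the previous 24 hours. It gives no response options and no total range. On data entry, the protocol says only that the system "captures entries via the telephone keypad" and that "The IVR program automatically blocks invalid responses and alerts the respondent that they need to make a valid entry".

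Every participant must meet the criterion "Current DSM-V diagnosis of PTSD". For the assessment-only (AO) arm, the section on check-ins and re-randomization also draws on the IVR data, without a point threshold: "Should marked clinical deterioration be noted either during a telephone check-in or via the daily IVR assessments", the participant is assessed for whether staying in the study is safe.

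**The concern.** A fixed absolute rise on a bounded score has a ceiling. Anyone who starts closer to the maximum than the required rise cannot meet the rule, however much they worsen. Those excluded are always the participants with the highest starting scores, and this trial enrols only people with current PTSD.

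Forty-seven points looks large for 20 items. If the range is narrow, the alert is out of reach for much of the scale; if it is wide, only the top is affected. The protocol does not let a reader tell which. At stake is the one numeric PTSD safety criterion in the document. The adverse events section also refers the reader back to the IVR monitoring section for ongoing safety monitoring.

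**Working it through.** The protocol gives no derivation of 47, so there is no figure of its own to reproduce. The check is ceiling arithmetic.

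**Inputs**

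- Required rise: 47 points (Daily IVR Monitoring).
- Number of items: 20 (Questionnaires, IVR row for the daily PTSD checklist).
- Link between the two: inferred. The trigger is read from call data, and this checklist is the only PTSD symptom score in those data. The CAPS is not collected by IVR, and the other PTSD-related IVR entry is a 3-item coping-efficacy measure.
- Response scale per item: not stated. Assumed, and shown as a range.

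**Formulas**

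- Average rise per item = 47 / 20 = 2.35 points.
- With items scored from 0 to h, the maximum total is 20 × h. The highest first-day score that can still trigger is 20 × h − 47.
- The largest possible rise from the midpoint of every item is 20 × h / 2.

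**Results**

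| Assumed item scale | Maximum total | Highest first-day score that can trigger | Share of range | Largest rise from midpoint | Mid-scale starter can trigger? |
|---|---|---|---|---|---|
| 0-3 | 60 | 60 − 47 = 13 | 22% | 30 | No |
| 0-4 | 80 | 80 − 47 = 33 | 41% | 40 | No |
| 0-6 | 120 | 120 − 47 = 73 | 61% | 60 | Yes |
| 0-8 | 160 | 160 − 47 = 113 | 71% | 80 | Yes |
| 0-9 | 180 | 180 − 47 = 133 | 74% | 90 | Yes |

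Scoring items 1-5 gives the same result as 0-4, shifted by 20: the range is 20 to 100 and the limit is 53, again 33 points above the floor.

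On five-step items the limit of 33 is an item mean of 33 / 20 = 1.65 on 0-4. With items scored only 0 or 2, 16 items at 2 give 32 and leave room for a rise of 48, so the alert is still reachable. Seventeen items at 2 give 34 and leave room for 46, so it is not.

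**The case against.** The strongest objection is that the result turns on a response scale that the protocol does not state. A telephone keypad allows many options, and with seven or more per item a mid-scale starter can trigger the alert. Only those in roughly the top 26% to 39% of the range cannot. The sentence with the 47 points also does not name the checklist. This stands, and it limits what can be concluded. It does not remove the problem: on every scale considered, some of the highest starters are shut out.

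A reader might infer more than the documents support, in four ways.

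- *That nobody with moderate or worse symptoms can trigger the alert.* This depends on the unstated scale, and the protocol does not define moderate on this checklist. Even on five-step items, a participant who marks the middle option on most items and zero on the rest is excluded only from 17 of 20 items upward.
- *That a known share of participants is excluded.* No first-day scores are given. A normal distribution with an assumed mean of 35 to 50 and SD of 15 on the 80-point range gives about 54% to 86%. The same assumptions doubled to fit a 160-point range give about 7% to 33%. A spread from 7% to 86% is not an estimate.
- *That excluded participants go unmonitored.* IVR data are reviewed on business days. AO participants get weekly calls, and deterioration is judged without a threshold. Therapy participants attend twice weekly and complete weekly measures that their therapists review. The discontinuation section also acts on deterioration without a score.
- *That a lack of alerts would be taken as a lack of deterioration.* Nothing says so; the safety monitors review adverse events, not alert counts.

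It is also fair to say that no rule based on a rise can be met from every first-day score, because a participant at the maximum cannot rise. That cannot be the standard for a corrected rule of the same type.

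**Conclusion.** The point holds as a defect in how the PTSD alert is specified. If the 47 points refer to the 20-item daily checklist, which the Questionnaires table makes the only plausible reading, the alert cannot fire for anyone starting within 47 points of the maximum. That means above 41% of the range on five-step items and above 74% on the widest keypad scale considered (0-9). The excluded group is always the most severe at the start of monitoring.

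The size between those limits cannot be settled from the protocol, and neither can the number of participants affected. The other safety routes reduce the consequence, but the weekly ones and the judgement-based ones do not make the daily numeric alert work for these participants. This is more than a missing detail, because following the rule exactly as written leaves the most severe starters without the only numeric PTSD alert.

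**What to change.** Reconcile the Daily IVR Monitoring section with the Questionnaires table:

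1. Name the instrument to which the 47 points refer, and state its response options and total range.
2. Check the 47-point figure against that range and report the first-day score above which it cannot be reached.
3. Have the sponsor's clinical team revise the criterion so that participants with high first-day scores are also covered. Its form and value are theirs to set.

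The cost is a short amendment, a change to the flag used in the daily review, and some additional follow-up calls.

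The overview of final modifications already reports enrolment and procedures in the past tense. If monitoring has ended, the amendment can no longer change practice. Any safety report that presents PTSD alerts should then state this ceiling beside them.
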